### Outcome assessment

#### Primary outcomes

The main outcome will be the difference before and after intervention in the percentage of participants meeting recommended levels of PA (at least 150 minutes at week of moderate to vigorous intensity) [1,2], between and within intervention and control groups. Based on previous experiences [20-23], the PA program (intervention) will be considered effective if it achieves an increase of 20% in the proportion of hypertensive patients in the intervention group defined as active compared to control group, at the end of the intervention (24 weeks) to evaluate adherence and at 32 weeks to assess the sustainability of intervention effects.

PA levels will be assessed at three time points during the study to determine changes in the following: percentage of participants meeting the PA recommendation, minutes of moderate and vigorous PA performed per week and minutes per day of sedentary behavior. In the intervention group, we will also measure change over time in the following tests of functional capacity: walking distance (6 minute walk test) [37], maximum heart rate and 1 minute heart-rate recovery [38]; these measurements will be taken at baseline, 24 and 32 weeks too. These variables will be used as a complementary assessment of participant’s functional capacity and not as the primary outcome of the study.

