#### Secondary outcomes

Outcomes assessed in the intervention and control groups at 24 and 32 weeks will be: a) blood pressure levels; b) biochemical markers: triglycerides, total cholesterol and HDL, fasting glucose; c) anthropometric measures: weight, BMI, hip and waist circumference to calculate waist/hip ratio; d) social/psychological measures: attitude towards PA participation based on Prochaska’s stages of change model [29], PA self-efficacy [39] health related quality of life (SF-12) [40], symptoms of depression (CESD, 20-item version) [41] and social support for PA participation.

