### Statistical analysis

Analysis of effectiveness will be carried out according to an intention to treat analysis.

A baseline comparability analysis will be carried out among the IG and CG, in relation to the variables studied during the three measurement points in the study (0, 24 and 32 weeks). To compare means, T-test or analysis of variance will be conducted, while Mann–Whitney tests will be used to compare variables without a normal distribution. Analysis of covariance will be conducted to assess variables with repeated measures along the study.

Longitudinal generalized mixed models will be developed to account for the repeated measurements (0, 24 and 32 weeks) for each patient. These models will be linear for continuous changes in PA (minutes), and logistic for categorical PA variables.

For the primary outcome variable, models will be adjusted for potential confounding variables that may alter the proportion of patients who meet the minimum recommendation for PA: a) geographic accessibility barriers (e.g. distance to SCC); b) financial (e.g. self-report of financial resources to pay for transportation); c) administrative (e.g. SCC schedules not being compatible with patient’s reported schedules); d) social support (e.g. help with transportation to the SCC); e) conditions of patient (for example: greater physical fitness than other hypertensive patients, discomfort or injury discouraging participation in the program, presence of acute or chronic diseases).

In order to minimize regression bias to the estimated mean, baseline values for each dependent variable will be included in each regression model [47].

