Evidence from self-reports indicates that referral schemes are effective in increasing PA as measured by self-reports. Yet, information on referral programs’ influence on patient’s PA, measured via objective method is lacking [22,54]. This study will be the first to use direct measurements of PA to show the effects of an exercise-referral scheme in real-world settings. Although we are aware of the limitations posed by the study’s short duration, this does not compromise its utility for physical activity promotion in patients with chronic conditions.

If this intervention is found to be effective, the information could useful to optimize resources. For example, to design programs according to different stages of change, proposing differentiated actions for patients in each one of the stages, as stated in the transtheoretical model [29]. Namely, carry out actions to encourage the willingness to change for patients in pre-contemplation stages or to strengthen their physically active behavior for patients in maintenance stage.

The study population is sharing characteristics such as initially sedentary lifestyle, willingness to engage in PA, and recent hypertension diagnosis. Sharing these traits could encourage the group to develop a sense of community which would promote self-efficacy and social support [55], a fundamental feature of successful behavior change according to social cognitive theory [35,36].

To ensure the quality of this study, the clinical trial guidelines developed by the CONSORT group will be followed [56]. We will be able to identify the number of patients at the three measurement phases of the study and conduct the analysis according to intention to treat.

Finally, this assessment of effectiveness in the real-life conditions of the IMSS health and social services facilities, will serve as a baseline for these types of intervention studies in the context of Latin America, where the ability to test the feasibility, adherence and sustainability of an exercise-referral scheme has not been explored.

While this study is an effort to try to improve participants’ health and the quality of life through PA promotion, we are aware that this kind of initiative does not address the root causes of physical inactivity. This problem will persist unless both PA behaviors and the causes of inactivity change, a situation which requires approaches focused not only on individual behavior, but also on complex population-level systems and interactions [57].

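### The primary-outcome models adjust for programme-related items and social support without limiting them to baseline values, and use week 0 as both modelled outcome and covariate

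*Protocol article*

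**What the plan says.** The Statistical analysis section promises an intention-to-treat analysis. For the primary outcome it then states that "models will be adjusted for potential confounding variables that may alter the proportion of patients who meet the minimum recommendation for PA". Five classes follow: (a) geographic access; (b) finances; (c) administrative barriers, such as an SCC timetable that does not suit the patient; "d) social support (e.g. help with transportation to the SCC"); and (e) patient conditions, which include better fitness than other patients and "discomfort or injury discouraging participation in the program, presence of acute or chronic diseases". No measurement time is given for any of them.

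Secondary outcomes lists "symptoms of depression (CESD, 20-item version) [41] and social support for PA participation" among the measures taken in both arms at 24 and 32 weeks. The Discussion says of the participants: "Sharing these traits could encourage the group to develop a sense of community which would promote self-efficacy and social support". Under Control group (CG), controls receive information and remain on usual care at their primary care unit (PHCU).

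On the baseline, the same section describes longitudinal mixed models for the measurements at 0, 24 and 32 weeks, linear for minutes and logistic for categories. To limit regression to the mean it adds that "baseline values for each dependent variable will be included in each regression model". It names no group-by-time term and no target contrast. Inclusion criterion d) admits only patients who fall short of the activity recommendation on the short IPAQ.

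**The concern.** Allocation is random, by PHCU. A variable that comes into being because a patient was referred cannot confound that allocation. Three listed items are worded in terms of the SCC or its programme: timetable clash, help with transport, and discomfort or injury that discourages participation. A control has no programme session to clash with, travel to or be put off from, so unless the item is asked of everyone at entry its value in controls is undefined or fixed at none. The covariate is then tied to arm. Social support, if the week-24 or week-32 value is used, lies on the path by which the protocol expects the programme to work.

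Conditioning on such values answers another question: the effect not running through social support, or the effect in IG patients without barriers. Neither is the intention-to-treat effect. Primary outcomes sets the criterion for effectiveness at a 20% increase in the proportion active, so a shift of several points could change the trial's conclusion.

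The second matter is week 0. There is no treatment effect at baseline, so a week-0 outcome row adds a null to any effect averaged over visits. Entering the same value as a covariate does not repair this.

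**Working it through.** The plan gives no figure for either point, so there is nothing to reproduce. The design rates of 17% and 37% come from Sample size. Every other input below is an assumption, marked as such.

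**1. Sorting the listed adjusters**
- Can be measured at entry in both arms: distance (Randomization reports 5.1 km for IG and 6.6 km for CG units), financial resources, pre-existing disease.
- Acceptable or not depending on timing: social support, fitness.
- Worded around the programme: timetable clash, transport help, and "discomfort or injury discouraging participation in the program".

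**2. Mediator.** If a share q of the effect runs through the adjusted variable, the adjusted difference is 20 × (1 − q) points.
- q = 0.25: 15 points
- q = 0.50: 10 points
- q = 0.75: 5 points

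The documents give no value for q.

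**3. Barrier recorded only in IG.** Assume it lowers the outcome by 25 points and is present in a share s of IG. IG overall is 37%, so IG patients without the barrier are at 37 + 25s. Against 17% in controls, the adjusted coefficient is 20 + 25s.
- s = 0.2: 25 points
- s = 0.4: 30 points
- s = 0.6: 35 points

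The bias is now upward.

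**4. Injury as a common consequence** of allocation and of an unmeasured frailty (assumed). In a large simulated sample, an unadjusted difference of 19 points became 19.4 to 22.3 after adjustment, depending on the strength of the links.

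**5. Week 0 as outcome and covariate, linear model, group main effect only.** With effect D at weeks 24 and 32 and complete data, the coefficient is (0 + D + D)/3 = 2D/3. A large simulated sample with D = 60 min/week gave 40.0; weeks 24 and 32 alone with the baseline covariate gave 60.0. With 200 simulated trials of 112 per arm, SD 60, correlation 0.5 and D = 50, the results were 33.3 and 50.0.

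**6. The same rows with group-by-time terms.** For D = 60 the group term was about 0 and the interactions were 59.9 and 60.2, so the effect is recovered. The baseline covariate is constant within a patient and cancels from the contrast, which is therefore a difference in mean change. For n patients per arm, ignoring clustering:
- change contrast: variance = 2σ²(1 − ρ) × 2/n
- ANCOVA: variance = σ²(1 − ρ²) × 2/n
- ratio = 2/(1 + ρ)

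At ρ = 0.5 the ratio is 2/1.5 = 1.33. At ρ = 0.3 it is 1.54 and at ρ = 0.7 it is 1.18.

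**7. IPAQ binary outcome.** By criterion d), nobody meets the recommendation at entry. So far as that reading serves as week 0, the binary baseline covariate is a constant and cannot be separated from the intercept. Averaged over three visits, 17% and 37% become 2 × 17/3 = 11.3% and 2 × 37/3 = 24.7%: 13.3 points instead of 20, or an odds ratio of 2.56 instead of 2.87. Those are the figures without a visit term. With visit as a factor, the week-0 log odds has no finite estimate, and a contrast against week 0 is undefined on the logit scale. Eligibility does not force the accelerometer outcome to zero at baseline.

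**The case against.** The article does not say that the covariates are taken after allocation. The section on demographic, health history and lifestyle measurements has questionnaires completed at three points, including baseline. Patients in all PHCUs are screened for willingness to join an activity programme, so timetable fit and transport help could be asked of controls at entry. With only two PHCUs per arm, imbalance in patient characteristics is likely and some adjustment is sensible. The social-support example in the covariate list is transport help, which need not be the scale used as a secondary outcome.

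On week 0, Primary outcomes defines a before-after difference at 24 and at 32 weeks. That points to visit-specific contrasts, for which there is no dilution. The choice of exact contrast is commonly left to an analysis plan.

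Most of this stands, and it rules out several stronger readings:
- A reader might infer that every listed adjuster is a post-allocation variable. Distance, finances and pre-existing disease need not be.
- A reader might infer that adjusting for fitness would drop the controls, because of "In the intervention group, we will also measure change over time in the following tests of functional capacity". That sentence concerns change over time. Baseline assessment includes functional capacity before the arms are described, so a baseline value may exist for both.
- A reader might infer that the model's group coefficient cannot be the effect of referral, or must be shrunk to two thirds. That needs a group main effect, which the article never states.

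What does not fall away is that the covariate list and the baseline rule are positive statements, not omissions. An injury that discourages participation in the programme is hard to defend as an entry characteristic common to both arms. An analysis plan that follows the section literally inherits both faults.

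**Conclusion.** The point holds as a fault of specification that should be corrected. Followed as written and without a baseline restriction, the adjustment conflicts with the promised intention-to-treat effect. The direction of bias is not determined and its size is unknown. The figures of 5 to 15 points and 25 to 35 points show only what assumed mediation shares and barrier frequencies would do; they do not predict this trial's result.

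For week 0, the consequence depends on the model chosen. A group main effect in the linear model would be diluted to two thirds. A group-by-time contrast would be unbiased on this account, but the baseline covariate would do nothing for it, at a variance cost of about 33% over ANCOVA if the correlation is 0.5 (18% to 54% for correlations of 0.7 to 0.3). The all-zero baseline concerns the IPAQ binary outcome only.

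**What to change.** - Adjust only for pre-specified covariates recorded at baseline, in the same way in both arms: distance, financial resources, pre-existing disease, baseline social support and, if measured in both arms, baseline fitness. Because PHCUs are randomized before any other activity, define baseline as entry, before the programme starts.
- Move SCC timetable, transport and injury items to a descriptive analysis of adherence within the IG.
- Use post-baseline visits only as outcome rows, with group, week and group-by-week terms and continuous baseline minutes of moderate-to-vigorous activity as covariate, for the binary outcomes too.
- Name the 24-week group contrast, and add a 32-week contrast for outcomes measured in both arms at that visit.
- Before specifying a 32-week accelerometer contrast, reconcile two sections. Control group (CG) invites controls to activity assessments at 24 and 32 weeks, whereas Physical activity measurement lists accelerometer categories for controls at baseline and 24 weeks only. If the latter stands, the 32-week contrast cannot be estimated for that outcome.

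The cost is revised wording in the analysis section and a check that the chosen baseline items are recorded in both arms. Only the week-32 accelerometer question could require further data collection.

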**Methods and design:**

We will describe the methods of a cluster randomized trial study designed to evaluate the effectiveness of an exercise referral scheme to increasing physical activity in hypertensive patients compared to a non-referral scheme. Four PHCU were selected for the study; the PHCU will take part as the unit of randomization and sedentary hypertensive patients as the unit of assessment. 2 PHCU of control group (GC) will provide information to hypertensive patients about physical activity benefits and ways to increase it safely. 2 PHCU of intervention group (IG) will refer patients to sports facilities at the same institution, to follow a group-based PA program developed to increase the PA levels with a designed based on the Transtheoretical Model and Social Cognitive Theory. To evaluate the effects of the intervention as well as short-term maintenance of the intervention’s effects, PA will be assessed at baseline, at 24 and 32 weeks of follow-up.

The main outcome will be the difference before and after intervention in the percentage of participants meeting recommended levels of PA between and within intervention and control groups. PA will be measured through self-report and with objective measure by accelerometer.

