a) Adults between 35 and 70 years old; b) both sexes; c) patients with hypertension diagnosis within five years or less and/or without pharmacological therapy for hypertension (according with JNC 7 criteria) [27]; d) Not meeting PA recommendations (<150 minutes at week of moderate or vigorous intensity), as measured with the short-form of the International Physical Activity Questionnaire (IPAQ) [28]; e) currently in the contemplation or preparation stage for PA, according to Transtheoretical model of behavioural change [29]; f) low to moderate level of cardiovascular risk, according to the Guidelines for exercise testing and recommendations of the American College of Sports Medicine (ACSM) [30]. A pre-participation screening questionnaire from American College of Sports Medicine (ACSM) and ACSM [31], will be used to evaluate health status, medical history of cardiovascular, metabolic or lung disease, signs or symptoms suggestive of these conditions and number of cardiovascular risk factors. Symptoms that require a complex evaluation will be confirmed by medical staff; g) blood pressure levels: systolic blood pressure levels ≤ 160 mm Hg or diastolic ≤ 100 mm Hg [32,33]; [h) Body Mass Index < 35; i) biochemical markers in the following ranges: total cholesterol ≤ 240 mg/dL, fasting glucose level ≤ 126 mg/dL, triglycerides ≤ 150 mg/dL; j) physical ability to participate in the PA program (without problems that may impede walking or other moderate intensity PA).

Exclusion criteria:

For both the control and intervention groups: currently reporting high levels of PA (> 300 minutes at week of moderate to vigorous intensity) [34], having previously attended a PA program at MSSI facilities. Criteria during PA sessions in the intervention group: systolic/diastolic blood pressure prior to PA sessions > 200/100 mm Hg or during the session > 250/115 mm Hg. The elimination criteria proposed are: less than 80% PA program attendance with or without incomplete information in one of the three data-collection points in the study.The study’s recruitment process is schematized in Figure 1. Patients who meet the criteria previously described will be invited to participate. Patients accepting to participate will provide informed consent and will be formally enrolled.

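### The baseline covariate for the yes/no activity outcome is constant or nearly so on the IPAQ and coarse on the accelerometer; baseline minutes should replace it

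*Protocol article*

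**What the plan says.** All references are to the protocol article.

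- **Outcome (Primary outcomes).** The main outcome concerns "the percentage of participants meeting recommended levels of PA (at least 150 minutes at week of moderate to vigorous intensity", so it is binary. The same section also lists minutes per week as an activity variable: "percentage of participants meeting the PA recommendation, minutes of moderate and vigorous PA performed per week and minutes per day of sedentary behavior".
- **Instruments (Abstract, Methods and design).** "PA will be measured through self-report and with objective measure by accelerometer". No single primary instrument is named. The Physical activity measurement section describes the yes/no classification step by step for the accelerometer only. It uses the IPAQ at screening and at the measurement points.
- **Entry (Design and recruitment process, criterion d).** The criterion reads: "Not meeting PA recommendations (<150 minutes at week of moderate or vigorous intensity), as measured with the short-form of the International Physical Activity Questionnaire (IPAQ".
- **Model (Statistical analysis).** "Longitudinal generalized mixed models will be developed to account for the repeated measurements (0, 24 and 32 weeks) for each patient", and "These models will be linear for continuous changes in PA (minutes), and logistic for categorical PA variables".
- **Baseline adjustment (Statistical analysis).** "In order to minimize regression bias to the estimated mean", the plan states that "baseline values for each dependent variable will be included in each regression model".

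**The concern.** The rule gives each model the baseline value of its own dependent variable. For the logistic model that variable is yes/no, so the natural reading is that the covariate is also yes/no. Criterion (d) selects patients at the same 150-minute threshold that defines success, on one of the two instruments that measure success. A covariate that selection has made the same for everyone cannot adjust for anything.

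On either instrument, a patient with 0 and a patient with 140 baseline minutes get the same covariate value, although one needs 150 more minutes to count as a success and the other needs 10. With only two PHCUs per arm, a difference between arms in baseline activity below the cut is plausible. The other adjusters listed (access, finance, schedules, social support, patient conditions) do not include baseline activity. What is at stake is some bias if the arms differ at baseline, and some lost precision.

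**Working it through.** The plan gives no figure for this adjustment, so there is none to reproduce. The inputs from the document are 17% vs 37%, 68 patients per group and a significance level of 0.05 (Sample size), and two PHCUs per arm. Everything else below is an assumption.

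**1. Is the covariate informative on the IPAQ?** If every patient has baseline status 0, the design matrix [1, arm, baseline status] has rank 2, not 3. The baseline coefficient cannot be estimated, and the arm estimate equals the unadjusted one. On the accelerometer the matrix had full rank in simulation, with 12% to 17% of patients meeting the threshold at baseline under the parameters in step 3.

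**2. Size of the bias, simple formula.** Assume a normal latent activity scale and an imbalance of δ SD in baseline minutes favouring the intervention arm. The unadjusted difference moves by Φ(Φ⁻¹(0.37) + rδ) − 0.37, where Φ⁻¹(0.37) = −0.332.

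| δ | r | Shift | Share of 20 points |
|---|---|---|---|
| 0.2 | 0.3 | 2.3 points | 11% |
| 0.2 | 0.5 | 3.8 points | 19% |
| 0.3 | 0.3 | 3.4 points | 17% |
| 0.3 | 0.5 | 5.8 points | 29% |

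This takes baseline minutes as error-free and untruncated.

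**3. How much does each covariate remove?** This simulation allows for measurement error: 400 runs, 112 per arm, no treatment effect (true odds ratio 1). It assumes log-normal usual activity with median 90 min and between-patient SD 0.8, error SD 0.6 for the IPAQ and 0.3 for the accelerometer, and entry at IPAQ below 150. Arms differ in usual activity by a shift in log units.

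| Shift | Instrument | Unadjusted OR | Binary baseline | Baseline minutes (log scale) |
|---|---|---|---|---|
| 0.15 | IPAQ | 1.21 | 1.21 | 1.13 |
| 0.15 | Accelerometer | 1.29 | 1.19 | 1.10 |
| 0.3 | IPAQ | 1.47 | 1.47 | 1.30 |
| 0.3 | Accelerometer | 1.67 | 1.42 | 1.20 |
| 0.5 | IPAQ | 1.77 | 1.77 | 1.46 |
| 0.5 | Accelerometer | 2.13 | 1.62 | 1.26 |

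At shift 0.3 on the log odds ratio scale:
- IPAQ: 0.388 unadjusted, 0.388 binary, 0.259 minutes. Minutes remove (0.388 − 0.259)/0.388 = 33%; the binary covariate removes nothing.
- Accelerometer: 0.514 unadjusted, 0.350 binary, 0.186 minutes. The binary covariate removes 0.164/0.514 = 32%; minutes remove 0.328/0.514 = 64%.

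With no shift, the three models gave 1.01, 1.01 and 1.01 on the IPAQ and 0.94 throughout on the accelerometer. The truth is 1 in both cases, so the 0.94 indicates the simulation error. Regression to the mean that is common to both arms does not bias the comparison between arms.

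**4. Power.** Latent difference Φ⁻¹(0.37) − Φ⁻¹(0.17) = −0.332 + 0.954 = 0.622; 68 per arm, two-sided 0.05, 1,500 trials per r, clustering ignored. The accelerometer columns assume that 17% meet the threshold at baseline.

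| r | IPAQ: no effective covariate | IPAQ: minutes | Accelerometer: binary | Accelerometer: minutes |
|---|---|---|---|---|
| 0.3 | 75.5% | 78.5% | 76.5% | 78.5% |
| 0.4 | 74.5% | 79.7% | 75.9% | 77.6% |
| 0.5 | 75.0% | 81.1% | 80.5% | 83.1% |
| 0.6 | 73.9% | 84.3% | 80.9% | 83.7% |

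The starting level near 75% agrees with the two-proportion formula for 68 per group. That this is not the 90% stated under Sample size is a separate matter.

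**5. Truncation at entry.** The IPAQ columns in step 4 do not truncate baseline. Cut the scale at its 83rd percentile (c = 0.954, density 0.253). Then λ = 0.253/0.83 = 0.305, and the variance is 1 − 0.954 × 0.305 − 0.305² = 0.616, so the SD is s = 0.785. With r′ = rs/√(r²s² + 1 − r²), r = 0.3 falls to 0.24 and r = 0.5 to 0.41. The IPAQ gains are therefore upper figures for a given r.

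**The case against.** The strongest objection is that the accelerometer, not the IPAQ, is the instrument that the article emphasises. Objective measurement is given as a reason for the study, and the accelerometer has the only described yes/no classification. Criterion (d) leaves its baseline free to vary. This stands. A reader might infer that the primary analysis has no baseline correction at all, and the documents do not support that: on the accelerometer the binary covariate removed about a third of the spurious effect in step 3.

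Three further points stand in part:

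- The text never says that the baseline is dichotomised, and the form of a covariate is often left to a fuller document. But the article does fix a rule. Its natural reading gives yes/no status, and that rule conflicts with the article's own entry criterion.
- If the IPAQ is repeated at week 0 after screening, some patients may reach 150 minutes. The covariate is then nearly, not strictly, constant.
- The calculations use one follow-up and patient-level models. The plan has mixed models with week 0 among the responses, and it adjusts for patient conditions, with fitness as an example. These could absorb part of an imbalance. However, on the IPAQ the week-0 responses are all, or nearly all, negative too, so they add little information on baseline activity.

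It is also tempting to say that adjusting for minutes restores the assumed 20-point difference. That needs error-free baseline minutes, and step 3 shows that it fails with measurement error.

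**Conclusion.** The point holds in a limited form. For the IPAQ version of the yes/no outcome, the stated baseline adjustment is empty or nearly so, and the arm estimate is effectively not adjusted for baseline activity. For the accelerometer version it works in part and loses information.

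The power lost is about 3 to 10 points on the IPAQ for r = 0.3 to 0.6, less after truncation, and about 2 to 3 points on the accelerometer. The bias matters only if the arms differ at baseline. Nothing in the documents shows that they do; two PHCUs per arm make it plausible. The correlations, imbalances and error sizes are assumptions, and clustering was not modelled.

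Baseline minutes also do not remove regression to the mean from the within-group before-and-after comparison, where the screening IPAQ baseline is 0% by selection. The change is worth making because it costs almost nothing, not because the present rule invalidates the primary analysis.

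**What to change.** Keep the binary primary outcome. Replace the covariate rule for the logistic models with, for example: *In the logistic models for meeting the PA recommendation, the baseline covariate will be continuous baseline minutes per week of moderate-to-vigorous PA from the same instrument, in place of baseline yes/no status. The responses will be those at weeks 24 and 32. The adjusted difference in proportions will be obtained by standardising over the observed baseline minutes.*

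Taking week 0 out of the responses avoids using it as both response and covariate. The Physical activity measurement section lists the week-32 accelerometer classification for the intervention group only, so on that instrument the sentence can apply at week 32 only once that schedule has been reconciled with the Control group section.

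The cost is one sentence. No new data are needed, since baseline minutes are already collected with both instruments. The small downside is that the adjusted odds ratio is conditional, which is why the difference in proportions needs standardisation.
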